### Statistical analyses

Demographic and baseline information will be described, and eye-specific characteristics will be described for either arm. To study the non-inferiority of ICL to SMILE, a 90% confidence interval (CI) of the difference in predictability between the two treatments (SMILE minus ICL) using a linear mixed model. If the upper limit of the 90% CI does not exceed the pre-defined non-inferiority margin of 2%, non-inferiority is confirmed. Similarly, for each of the two secondary outcomes, efficacy, and safety, a 90% CI of the difference between the two treatments using the above-mentioned method will be constructed and then compared with a non-inferiority margin of 2%. Assuming the other secondary outcome, HOA, follows a normal distribution, a 90% CI of the difference between the two treatments will be constructed through the linear mixed model, and then compared with a non-inferiority margin of 2%. All the statistical analyses of the data will be performed using SPSS 23.0 (Inc, Chicago, IL) package. Normality of data will be examined by histogram frequency analysis and the Shapiro–Wilk test. Data will be presented as the mean ± standard deviation (SD) for continuous variables. Student’s *t*-test and ANOVA for normally distributed variables or Mann–Whitney *U* test for skewed distributions will be used to compare differences, while the proportion for categorical data and chi-squared or Fisher’s exact test to test statistical significance. All statistical tests used a 2-sided *P* value of 0.05.

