### Outcomes and trial duration

All patients are assessed at baseline, 1, 3, 6, 12, and 18 months. We plan to use standard primary and secondary outcomes measures at 3 months postoperatively, which is reported as standard outcomes in refractive studies. The primary outcome is the refractive predictability at each time point after surgery, which is the proportion of the number of eyes achieving a postoperative spherical equivalent (SE) within ± 0.5 D and ± 1.0 D of the intended target [5]. Secondary outcomes included.Unaided visual acuity (UDVA) and best corrected visual acuity (CDVA) following surgery in the study eye using the Snellen chart at a starting distance of 6 m.Refraction (measured dioptric spherical equivalent, myopia, and astigmatism).Refractive astigmatism measured by refraction and corneal astigmatism based on the keratometry readings from the Pentacam corneal topography.Quality of vision as assessed by ocular high-order aberrations (HOAs) using the iTrace system.Changes in corneal endothelial cell count, intraocular pressure, and lens vault.

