### Sample size

As this is a non-inferiority trial with a binary outcome, we have calculated the required sample size using the maximum likelihood method for a large sample [20]. A review of the current literature reveals that the reported refractive predictabilities in ICL and SMILE range from 90.0% [12] to 97% [15] and from 93% [4] to 99% [5], respectively. We therefore assumed the refractive predictabilities in ICL and SMILE in this study are 95% and 97%, respectively. Thus, a sample size of 200 subjects (400 eyes) was deemed to be sufficient to confirm non-inferiority with a power of ≥ 80% and at a 5% significance level using a 2% non-inferiority margin, which is the clinically significant difference from our preliminary data. To account for a lost to follow-up rate of 30%, 300 subjects will be recruited instead of 200. Patients will be recruited for this trial through two primary mechanisms: local advertising and research patient database. Local advertising takes advantage of the audio-visual media as well as internet social platform. The Xi’an AIER refractive error patient registry (database) has been maintained since 2017 and currently contains more than ten thousand patients (more than 12 million people now live in the city).

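### The linear mixed model interval for the binary primary outcome runs slightly above its 5% error level at the planned rates, and clearly above it if success rates approach 99%

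*Protocol article*

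**What the plan says.** Under Outcomes and trial duration, the primary outcome is "the proportion of the number of eyes achieving a postoperative spherical equivalent (SE) within" a stated distance of target, so each eye is a success or a failure. The Sample size section agrees, opening with "As this is a non-inferiority trial with a binary outcome". It takes rates from the literature that "range from 90.0% [12] to 97% [15] and from 93% [4] to 99% [5], respectively" for ICL and SMILE, and then "assumed the refractive predictabilities in ICL and SMILE in this study are 95% and 97%, respectively". The test is to be made "at a 5% significance level using a 2% non-inferiority margin".

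The Statistical analyses section takes the deciding 90% interval for "the difference in predictability between the two treatments (SMILE minus ICL) using a linear mixed model". ICL is declared non-inferior if the upper limit is no more than 2%, which is a one-sided 5% test. The section applies the same method to efficacy and safety, and the same model to higher-order aberrations, for which it assumes normality. For the primary outcome it names no binary link, robust variance or score-type interval.

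**The concern.** At the planned rates, 200 eyes per arm would yield about 200 × 0.03 = 6 SMILE failures and 200 × 0.05 = 10 ICL failures. With so few events, the estimated difference and its standard error move together. If ICL happens to have few failures, the estimate shifts in its favour and the Gaussian interval also shortens. Both push the upper limit below 2%.

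At stake is the error rate of the trial's main claim. A rule presented as a 5% test may declare non-inferiority too often, and with equal arms the excess lies in the direction of the conclusion the trial hopes to reach.

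**Working it through.** **Inputs from the protocol article.** Planned rates of 97% (SMILE) and 95% (ICL); margin 2 points; upper limit of a 90% interval; 200 evaluable subjects with 400 eyes; 300 recruited with 30% loss. This gives 100 per arm evaluable as planned, 300 × 0.7 / 2 = 105 per arm after the stated loss, and 150 per arm with no loss.

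**Assumptions.** 1:1 allocation; one time point; both eyes analysed; inter-eye correlation 0, 0.3, 0.5 and 0.8, because the article gives none.

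**The plan's own figure.** The 200 subjects cannot be reproduced. The sample-size formula divides by (margin − assumed difference)² = (0.02 − 0.02)² = 0. That is a separate fault. It does mean that the planned rates lie exactly on the non-inferiority boundary, so any pass at 97/95 counts as a false positive at the worst point of the null.

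**Mechanism.** Take 200 eyes per arm, treated as independent for illustration. The simple Gaussian limit is d + 1.645 × √[pS(1−pS)/200 + pI(1−pI)/200], where d = pS − pI.

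- 2 failures in each arm: 0 + 1.645 × √(2 × 0.01 × 0.99 / 200) = 1.645 × 0.00995 = 1.64%, a pass. The score limit is 2.09%, not a pass.
- 1 SMILE and 2 ICL failures: 0.005 + 1.645 × √[(0.005 × 0.995 + 0.01 × 0.99) / 200] = 0.005 + 1.645 × 0.00862 = 1.92%, a pass. The score limit is 2.53%, not a pass.

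The score method evaluates the variance with the difference held at the value being tested. At a difference of 2 points the ICL failure rate must be at least 2%, so its standard error cannot collapse.

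**Linear mixed model in closed form.** For balanced pairs of eyes at one time point, the REML random-intercept interval has upper limit d + t(0.95) × √[(MSB/2)(1/nS + 1/nI)]. MSB is the between-participant mean square, pooled with the within-participant mean square if the estimated correlation is negative.

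**Comparator.** A Farrington-Manning score test at 0.02, with variance multiplied by 1 + estimated inter-eye correlation, passing if z ≤ −1.645.

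**False non-inferiority at a true difference of 2 points.** 200,000 runs per cell; the Monte Carlo standard error is √(0.05 × 0.95 / 200,000), about 0.05 points. Ranges are over the four correlations.

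| SMILE/ICL | Linear, 100 per arm | Linear, 105 | Linear, 150 | Clustered score, all three sizes |
|---|---|---|---|---|
| 95/93 | 5.0–5.5% | 5.0–5.6% | 5.1–5.4% | 4.6–5.1% |
| 97/95 (planned) | 5.3–6.1% | 5.5–6.2% | 5.3–5.9% | 4.5–5.0% |
| 99/97 (tops of ranges) | 7.4–9.3% | 7.7–9.4% | 6.7–8.3% | 4.3–5.1% |

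At 93/91 the linear model gives 4.9–5.3% (100 or 150 per arm, correlation 0 to 0.7).

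**Unequal evaluable arms (assumed sizes), linear model.** At 97/95: 4.9–5.7% with 90 SMILE and 120 ICL participants, and 6.2–6.6% with 120 and 90. At 99/97: 6.1–8.5% and 8.5–10.6% respectively.

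**The case against.** Much of the case on the other side stands. The linear mixed model estimates the risk difference directly, on the scale of the margin, and can allow for two eyes per participant. The quantity estimated is right, and only the interval is weak near the ceiling. At the planned rates the excess is about one point or less, and in the lower part of the cited ranges it nearly vanishes.

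A reader might infer four stronger things that the article does not support:

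- That the outcome is planned near 97 to 99%. It is planned at 95% and 97%; 97% and 99% are only the tops of the two literature ranges.
- That the error level roughly doubles. That needs both arms at those tops. Still higher pairs, such as 99.5/97.5, lie beyond anything cited. The ±1.0 D window cannot have a lower success rate than ±0.5 D, so it could fall in this region, but the article gives no rate for it.
- That the model is always too lenient. With fewer SMILE than ICL participants the excess can disappear, and the 30% loss allowed for makes unequal arms plausible. The opposite imbalance makes it worse.
- That planning and analysis conflict. The Sample size section says "we have calculated the required sample size using the maximum likelihood method for a large sample", citing a source that is not at hand. Sizing with a large-sample binary formula and analysing with a model that handles clustering is common and not an error in itself.

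It could also be said that estimation details belong in an analysis plan. That does not dispose of the point, because the article itself names the model and the decision rule.

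**Conclusion.** The concern holds, with limited size. With equal arms, the stated rule has a one-sided error of about 5.3 to 6.2% at the planned rates instead of 5%. It is roughly nominal at 95/93 or lower, and about 7 to 9% in the sensitivity case of 99/97. These figures rest on an assumed inter-eye correlation of 0 to 0.8, equal allocation, two eyes per participant and a single time point.

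Severity is minor to moderate: small where the plan expects to be, material only if success rates turn out near 99%. The assumed difference equalling the margin is a separate and larger fault; repairing either one does not repair the other.

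**What to change.** For the binary primary endpoint, and for efficacy and safety if they are analysed as proportions, replace the linear mixed model interval with a 90% risk-difference interval that is valid near 100% and treats the participant as the cluster. One option is a Farrington-Manning or Miettinen-Nurminen score interval with variance inflated by 1 + the estimated inter-eye correlation. That factor is for two eyes per participant and needs adapting if some contribute only one. Another clustered binary method would serve, such as a binomial GEE or mixed model with marginal standardisation and a small-sample correction, provided simulation shows that it holds the 5% level. Keep the linear mixed model for continuous outcomes.

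The cost is some programming outside standard menus and a lower chance of declaring non-inferiority. With 100 participants per arm and correlation 0.5, it is about 23% instead of 28% when both arms are truly 97%. The gap widens to about 41% versus 57% when both are 99%, which is the region where the linear interval is too short.

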## Abstract

**Background:**

Implantable collamer lens implantation (ICL) is a form of ‘foldable’ posterior chamber phakic intraocular lens refractive surgery that generally does not impair cornea and natural accommodation. The potential advantages of the ICL over keratorefractive laser procedures include less induction of higher-order aberrations (HOAs) and enhanced retinal image magnification. On the other hand, small incision lenticule extraction (SMILE), currently, one of the most popular refractive surgery procedures, also offers excellent visual outcomes, particularly for eyes with low to moderate amounts of myopia. The aim of this study is to evaluate whether ICL/TICL (toric ICL) is comparable to SMILE for low to moderate myopia in terms of refractive outcomes at 3 and 18 months post-operatively.

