### Baseline assessment

At baseline all patients were assessed as follows:Visual acuity (unaided and corrected), Snellen Chart at a starting distance of 6 m (m) in both eyes.Subjective refraction, both eyes.Corneal tomography and corneal center thickness, Scheimpflug imaging (Pentacam) in both eyes.High-order aberration, ray-trace imaging (iTrace) in both eyes.

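### The HOA analysis names no baseline term although HOA is measured preoperatively in both eyes; stating baseline adjustment would gain precision by an amount the documents do not fix

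*Protocol article*

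**What the plan says.** The Baseline assessment section of the protocol article lists "High-order aberration, ray-trace imaging (iTrace) in both eyes". Outcomes and trial duration then makes the same measurement a secondary outcome: "Quality of vision as assessed by ocular high-order aberrations (HOAs) using the iTrace system". Visits are set there too: "All patients are assessed at baseline, 1, 3, 6, 12, and 18 months". The Abstract gives the reason for interest in HOA: "potential advantages of the ICL over keratorefractive laser procedures include less induction of higher-order aberrations (HOAs".

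Statistical analyses specifies the comparison: "HOA, follows a normal distribution, a 90% CI of the difference between the two treatments will be constructed through the linear mixed model", with the result set against a margin of 2%. It lists no covariate, random effect or visit term. The only stated use of baseline data is descriptive: "Demographic and baseline information will be described, and eye-specific characteristics will be described for either arm".

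The secondary outcomes also include changes in endothelial cell count, intraocular pressure and lens vault. None of these is assigned a mixed model. The general list of methods for continuous data is Student's t-test and ANOVA, or Mann-Whitney for skewed data.

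**The concern.** For a continuous outcome measured with the same instrument before and after surgery, the eye's own baseline is usually the most useful covariate available. If it is left out, between-person variation in preoperative HOA stays in the error term, and any chance difference between the arms at baseline carries into the estimate. Non-inferiority on HOA is to be judged from a confidence limit, so the width of the interval affects the conclusion.

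Naming the baseline term in advance also removes a later choice between an unadjusted level, a change score and an adjusted level, which can give different intervals from the same data.

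For cell count and pressure, a t-test or Mann-Whitney test on change scores uses the baseline by subtraction only and cannot adjust for it. ANOVA could be extended with a covariate, but none is named.

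**Working it through.** **Is there a plan figure to reproduce?** Not for HOA. Sample size covers the binary primary outcome only ("We therefore assumed the refractive predictabilities in ICL and SMILE in this study are 95% and 97%, respectively"). No SD, correlation, power or sample size is given for HOA, cell count or pressure.

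**Inputs**
- From the Sample size section: 200 subjects before allowance for dropout.
- Assumed: 1:1 allocation (100 per arm), one value per participant, equal variances before and after surgery, and ρ from 0.1 to 0.7.

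**Step 1. Adjusted against unadjusted postoperative HOA.** The variance ratio is 1 − ρ² and the CI width ratio is √(1 − ρ²). Neither depends on the sample size. Without adjustment, the 90% CI half-width at 100 per arm is 1.645 × √(2/100) = 0.233 SD. The equivalent unadjusted sample per arm is 100/(1 − ρ²).

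| ρ (assumed) | Variance saved | CI width ratio | 90% CI half-width (SD) | Equivalent unadjusted n per arm |
|---|---|---|---|---|
| 0.1 | 1% | 0.995 | 0.231 | 101 |
| 0.3 | 9% | 0.954 | 0.222 | 110 |
| 0.5 | 25% | 0.866 | 0.202 | 133 |
| 0.7 | 49% | 0.714 | 0.166 | 196 |

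**Step 2. What this could mean for power (illustration only).** Suppose the unadjusted comparison had 80% power at one-sided 5%, an assumption with no source in the documents. Adjusted power is then Φ((0.8416 + 1.645)/√(1 − ρ²) − 1.645):
- ρ = 0.1: 80%
- ρ = 0.3: 83%
- ρ = 0.5: Φ(2.4866/0.866 − 1.645) = 89%
- ρ = 0.7: 97%

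**Step 3. Chance imbalance.** At 100 per arm, the standard error of the between-arm difference in baseline means is √(2/100) = 0.141 SD. An imbalance of that size shifts the unadjusted estimate by ρ × 0.141 SD, for example 0.5 × 0.141 = 0.07 SD at ρ = 0.5. Adjustment removes this shift. Its average over randomizations is zero, so it is noise and not bias.

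**Step 4. A change score is not an equal substitute.** Relative to the unadjusted postoperative comparison, the variance of a change score is 2(1 − ρ): 1.4 at ρ = 0.3, 1.0 at 0.5 and 0.6 at 0.7. Below ρ = 0.5 it is worse than ignoring the baseline.

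**Step 5. Cell count and pressure.** Moving from a change score to covariate adjustment gives a variance ratio of (1 − ρ²)/(2(1 − ρ)) = (1 + ρ)/2. From an assumed 80% power at two-sided 5%, adjusted power is Φ((0.8416 + 1.96)/√((1 + ρ)/2) − 1.96):
- ρ = 0.5: ratio 0.75, power 90%
- ρ = 0.8: ratio 0.90, power 84%

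**The case against.** The strongest reply is that silence is not exclusion. The article names a linear mixed model and stops there. Such a model can carry baseline as a covariate or as one of the repeated measurements, and model terms for a secondary outcome are often left to a fuller protocol or analysis plan, neither of which is shown. This stands. A reader might infer that the trial has committed to an unadjusted postoperative comparison and is throwing away precision; the text does not say so.

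A reader might also infer, from the emphasis on induced aberrations, that a comparison of postoperative levels answers the wrong question. It does not. Randomization makes expected baseline HOA equal in the two arms, so the expected difference in postoperative HOA equals the expected difference in induced HOA. The adjusted model targets the same quantity.

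The size of the gain is also open. Both procedures may alter HOA, so ρ could be low and the benefit negligible. Moreover, the 2% margin has no defined scale for a continuous HOA measure. That is a separate problem, and it means actual HOA power cannot be computed with or without adjustment.

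For cell count and pressure, baseline does enter through the change, and the list of tests is generic. Baseline assessment lists neither measurement. A preoperative cell count is implied by the eligibility threshold in Table 1, and a preoperative pressure only because a change requires one. These replies limit the point but do not remove it: no method named for these outcomes is stated to include a baseline covariate.

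**Conclusion.** The point holds as a modest improvement to continuous secondary outcomes. Baseline HOA is collected in both eyes, and the stated analysis names no use of it beyond description. The comparison as written is valid and unbiased; what is at stake is CI width and protection against chance imbalance.

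The saving in variance runs from 1% at ρ = 0.1 to 49% at ρ = 0.7, with 25% at ρ = 0.5. These figures rest on an assumed correlation, 1:1 allocation and one value per participant. The power figures also rest on an assumed 80% starting point and should not be read as this trial's power. The documents do not support a claim that precision has been lost by a known amount, or that the HOA estimate is wrong.

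**What to change.** In Statistical analyses, state that the linear mixed model for postoperative HOA includes the same eye's baseline HOA as a prespecified covariate and a participant random effect for the two eyes, and that the 90% CI is that of the adjusted treatment difference. Use the same form of model for endothelial cell count, with the screening count as baseline, and for intraocular pressure where the preoperative value is recorded, in place of the t-test or Mann-Whitney test. Lens vault is left out because it has no preoperative value.

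The cost is one or two sentences. Baseline HOA is already collected, so its adjustment needs no extra visits, participants or measurements. For pressure, it should be confirmed that the preoperative value is in the dataset. The wording should be settled before these outcomes are examined by arm.

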## Methods/design

### Study design and randomization

This is a prospective, randomized controlled trial performed at Xi’An AIER eye hospital. The study adheres to the tenets of the Declaration of Helsinki and is registered at the Chinese clinical trial registry (ChiCTR2200055372) and used the SPIRIT reporting guidelines [19]. It was approved by the Xi’An AIER eye hospital ethics committee (AIER-Xian-2018001). Inclusion and exclusion criteria are shown in Table 1. Randomization will be performed on the day of surgery using a web-based, online, sealed envelope-based system (https://www.sealedenvelope.com). Specific study information sheets will be provided to patients prior to taking consent. Following a dedicated screening and randomization visit for eligible patients, participants will be randomized to one of two trial arms (Fig. 1) and then followed for 18 months at 1, 3, 6, 12, and 18 months (Fig. 2). Face-to-face adherence reminder sessions will take place at the initial trial and subsequent sessions will occur at the follow-up visits. To enhance adherence, simple strategies will be used including mobile phone or WeChat reminder service for participants at follow-up time. Because of the nature of the intervention, surgeon and participant masking will not be possible, so follow-up measurements will be performed by masked optometrists. The retreatment (secondary surgery) for refractive regression will not be permitted for all participants during the trial. However, after 18 months, retreatment must be performed for patients after refraction is stabilized. This protocol is the second version and is revised on Jan 2022. Recruitment commenced on May 2018, and the follow-up of the last recruited patient will be estimated to complete on Dec 2022.

**Table 1 Tab1:** Inclusion and exclusion criteria for trial participants

**Inclusion criteria**	21 years of age or older
	Spherical equivalent of ≤ -6.00 D
	Refractive cylinder ≤ -2.00 D
	Best spectacle-corrected visual acuity (BCVA) of 20/40 or better
	Spherical or cylindrical error has progressed at − 0.50 D or less per year before the baseline measurement
	Contact lens must have been removed at least 2 weeks before the baseline measurement
	No evidence of irregular astigmatism on corneal tomography
	Anterior chamber depth ≥ 2.8 mm
	Corneal endothelial cell count ≥ 2000/mm^2^
**Exclusion criteria**	Progressive or unstable myopia and/or astigmatism
	Clinical or corneal topographic evidence of keratoconus

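### Eye-level secondary outcomes outside the mixed model are left to independent-sample tests, although participants are randomised and two eyes each are counted

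*Protocol article*

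**What the plan says.** All references are to the protocol article.

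- **Unit of randomisation.** Study design and randomization: "participants will be randomized to one of two trial arms". Both eyes of a person are therefore in the same arm.
- **Unit of counting.** Sample size: "a sample size of 200 subjects (400 eyes) was deemed to be sufficient", which is two eyes per person. Outcomes and trial duration defines the primary outcome as "the proportion of the number of eyes achieving a postoperative spherical equivalent (SE) within" the stated limits of target.
- **Unit of measurement.** Baseline assessment records acuity, refraction, tomography and aberrations in both eyes, for example "Subjective refraction, both eyes". Outcomes and trial duration, however, describes visual acuity "in the study eye using the Snellen chart at a starting distance of 6 m", which is singular.
- **Methods.** Statistical analyses gives a linear mixed model with 90% confidence intervals to predictability, efficacy, safety and higher-order aberrations. It then names Student's t-test and ANOVA for normally distributed variables and Mann-Whitney "for skewed distributions will be used to compare differences, while the proportion for categorical data and chi-squared" or Fisher's exact test, all at two-sided 0.05. It does not say which outcomes these tests serve, whether the unit is the eye or the participant, or how fellow-eye correlation is handled in them.

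**The concern.** The listed tests take every observation as independent. Two eyes of one person that had the same procedure tend to give similar results, so a second eye adds less information than a second person would. Because both eyes are in the same arm, a positive correlation makes the true standard error of the arm difference larger than the one these tests compute.

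The secondary outcomes with no other stated method are refraction, refractive and corneal astigmatism, endothelial cell count and intraocular pressure. Visual acuity joins them if it is not what the plan means by efficacy or safety. Astigmatism and refraction bear on comparative accuracy, and cell count and pressure on the risks of the intraocular procedure. A difference in any of these could be declared significant more often than the stated 5%.

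This goes beyond detail that an article leaves to an analysis plan. The article itself chooses the tests, and they do not suit data with two eyes per participant.

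**Working it through.** **Inputs from the protocol.** Randomisation by participant (Study design and randomization); 200 subjects and 400 eyes (Sample size); two-sided 0.05 (Statistical analyses).

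**Assumptions.** The inter-eye correlation ρ is not given, so it is shown over a range. Allocation is taken as 1:1, since no ratio is stated.

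**The plan's own figure.** 200 subjects × 2 eyes = 400 eyes, so the count rests on two eyes from everyone. The plan states no error rate for these tests beyond the nominal 5%. Whether 400 eyes give the stated power is a separate question that this point does not use.

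**Step 1: variance.** With two eyes per participant in the same arm, the variance of an arm mean is multiplied by the design effect 1 + ρ. A test that ignores pairing understates the standard error by the factor √(1 + ρ).

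**Step 2: actual error.** Actual two-sided error = 2 × [1 − Φ(1.96 / √(1 + ρ))]. Equivalent independent eyes = 400 / (1 + ρ).

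| Assumed ρ | √(1 + ρ) | 1.96 / √(1 + ρ) | Actual error | Equivalent independent eyes |
|---|---|---|---|---|
| 0.1 | 1.049 | 1.869 | 6.2% | 364 |
| 0.3 | 1.140 | 1.719 | 8.6% | 308 |
| 0.5 | 1.225 | 1.600 | 11.0% | 267 |
| 0.8 | 1.342 | 1.461 | 14.4% | 222 |
| 0.9 | 1.378 | 1.422 | 15.5% | 211 |

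The error rate depends on ρ and on having two eyes per person, not on the number recruited, so enrolling 300 instead of 200 does not remove it.

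**Step 3: simulation.** No true difference, 100 participants (200 eyes) per arm, both eyes analysed as independent. Binary outcomes were run at assumed success rates of 80% and 96%; the two figures in a cell are in that order.

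| ρ | t-test | Mann-Whitney | Chi-squared | Fisher |
|---|---|---|---|---|
| 0.3 | 8.3% | 7.7% | 8.7%, 8.5% | 6.7%, 5.3% |
| 0.5 | 11.0% | 11.1% | 11.2%, 10.6% | 8.9%, 6.8% |
| 0.8 | 14.4% | 14.3% | 14.6%, 14.6% | 12.1%, 9.9% |

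At ρ = 0 the t-test, Mann-Whitney and chi-squared all gave about 5%, and Fisher 3.9% and 2.5%. The formula therefore describes the first three. Fisher starts below 5%, and this offsets part of the inflation. A one-way ANOVA of two arms is the t-test squared and has the same error.

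**The case against.** The strongest case against is that Statistical analyses never says these tests are run on eyes. The sentence names no outcome and no unit, and it would also fit demographic or other participant-level comparisons. The singular eye in the acuity definition even suggests one eye per person, and then there would be no inflation. This stands in part. Per-eye use is an inference from the 400-eye count, the eye-based primary outcome and the both-eyes measurements, so the error rates are conditional. It does not remove the point: if one eye is analysed, the 400-eye count is wrong, and if both are, the tests need replacing. The text must change either way.

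A reader might infer several stronger claims that the document does not support:

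- **That all eye-level results, including the primary one, are affected.** Predictability, efficacy, safety and higher-order aberrations are assigned to a linear mixed model, which can carry a participant effect.
- **That acuity is certainly outside the mixed model.** Efficacy and safety are not defined in the outcome list and may be based on acuity.
- **That baseline values are ignored.** Endothelial count and pressure are specified as changes, which use the baseline. An unadjusted randomised comparison is valid in any case.
- **That repeated visits are ignored.** ANOVA may be meant for comparisons across visits; the article does not say.
- **That Fisher's test is inflated as much as the others.** The simulation shows that it is not.

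**Conclusion.** The point holds for eye-level secondary outcomes that the plan does not assign to the mixed model, and only if both eyes enter the listed tests. On that condition, a nominal 5% two-sided test has an actual error of about 8.6% to 14.4% for the t-test, Mann-Whitney and chi-squared at assumed inter-eye correlations of 0.3 to 0.8, roughly two to three times nominal. For Fisher the range is about 5.3% to 12.1%. The correlations are assumptions, since the protocol reports none. The primary non-inferiority conclusion is not touched by this point. The change should be made because the tests as named would give wrong p-values on the eyes as counted, and the remedy is already in use elsewhere in the plan.

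**What to change.** 1. Analyse every eye-level outcome with a mixed model, or GEE, clustered on participant, so that the two eyes of one person are not treated as independent.
2. Restrict the t-test, ANOVA, Mann-Whitney, chi-squared and Fisher tests to variables with one value per participant.
3. Reconcile the acuity wording in Outcomes and trial duration with the count in Sample size. Either refer to both operated eyes, or name one eye per participant by a fixed rule and drop the 400-eye count.
4. State which listed outcomes efficacy and safety refer to, so that it is clear which model acuity falls under.

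Adjusting for the baseline value of the same measure is an optional gain in precision and not part of the error.

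The cost is a little more analysis work, with no new data, using a type of model that the plan already intends to fit. Some secondary p-values will be less favourable.
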